# The Sigma-trial protocol: a prospective double-blind multi-centre comparison of laparoscopic versus open elective sigmoid resection in patients with symptomatic diverticulitis

**DOI:** 10.1186/1471-2482-7-16

**Published:** 2007-08-03

## Abstract

**Backround:**

Diverticulosis is a common disease in the western society with an incidence of 33–66%. 10–25% of these patients will develop diverticulitis. In order to prevent a high-risk acute operation it is advised to perform elective sigmoid resection after two episodes of diverticulitis in the elderly patient or after one episode in the younger (< 50 years) patient. Open sigmoid resection is still the gold standard, but laparoscopic colon resections seem to have certain advantages over open procedures. On the other hand, a double blind investigation has never been performed. The Sigma-trial is designed to evaluate the presumed advantages of laparoscopic over open sigmoid resections in patients with symptomatic diverticulitis.

**Method:**

Indication for elective resection is one episode of diverticulitis in patients < 50 years and two episodes in patient > 50 years or in case of progressive abdominal complaints due to strictures caused by a previous episode of diverticulits. The diagnosis is confirmed by CT-scan, barium enema and/or coloscopy.

It is required that the participating surgeons have performed at least 15 laparoscopic and open sigmoid resections. Open resection is performed by median laparotomy, laparoscopic resection is approached by 4 or 5 cannula. Sigmoid and colon which contain serosal changes or induration are removed and a tension free anastomosis is created. After completion of either surgical procedure an opaque dressing will be used, covering from 10 cm above the umbilicus to the pubic bone. Surgery details will be kept separate from the patient's notes.

Primary endpoints are the postoperative morbidity and mortality. We divided morbidity in minor (e.g. wound infection), major (e.g. anastomotic leakage) and late (e.g. incisional hernias) complications, data will be collected during hospital stay and after six weeks and six months postoperative. Secondary endpoints are the operative and the postoperative recovery data. Operative data include duration of the operation, blood loss and conversion to laparotomy. Post operative recovery consists of return to normal diet, pain, analgesics, general health (SF-36 questionnaire) and duration of hospital stay.

**Discussion:**

The Sigma-trial is a prospective, multi-center, double-blind, randomized study to define the role of laparoscopic sigmoid resection in patients with symptomatic diverticulitis.

## Background

Diverticulosis is a common disease in the western society with an overall incidence of 33% in the population > 45 years of age and increasing to 66% in the population older than 85 years of age [1,2]. 10–25% of patients with diverticulosis will develop diverticulitis [3,4]. Treatment of diverticulitis is based on the severity of the disease, which can be staged by the Hinchey criteria, shown in table 1[5-8]. Most patients with stage I and II disease can be treated conservatively with bed rest, starvation, intra venous fluids and intra venous antibiotics. Abscesses greater than 5 cm are drained percutanously. In case of clinical decline of the patient or patients with stage III and IV disease, acute surgical intervention is indicated [5-8]. The inflamed bowel, mostly the sigmoid, has to be resected with or without creating a primary anastomosis. Mortality in these patients is relatively high, 6 to 22%, due to the severity of the disease [8].

**Table 1 T1:** Hinchey stage for diverticulitis.

I	Acute phlegmonous diverticulitis without complications
II	Diverticulitis with parcolic abscess without perforation
III	Diffuse purulent peritonitis
IV	Diffuse faecal peritonitis

The chance of developing a second episode of diverticulitis within five years after a successfully conservative treatment is 30% [6,9]. In order to prevent a high-risk acute operation it is therefore advised to perform an elective (sigmoid) resection of the affected bowel after two episodes of conservatively treated diverticulitis in the elderly patient or after one episode in the younger (< 50 years) patient. When the acute phase of the diverticulitis has calmed the resection can be performed, which will mostly take place after 3 months, resulting in a mortality rate of 2%.

Also patients with complaints such as pain, recurrent bleeding and important change of bowel movements due to stenosis of the sigmoid after an episode of diverticulitis may require an elective resection of the sigmoid.

Resection of the sigmoid by an open procedure is still the gold standard but it is also feasible to perform a laparoscopic sigmoid resection [10-14].

Because laparoscopic colon resections seem to have important short term advantages (less complications, less post-operative pain, less wound infections, shorter hospital stay and faster recovery) over an open procedure, the aim of this study is to compare, in terms of post-operative morbidity, mortality and quality of life, the laparoscopic resection of the sigmoid with an open resection in those patients in which an indication exist for an elective resection [15-18].

## Method

### Study objectives

The objective of this study is to define the role of laparoscopic treatment in patients with symptomatic diverticulitis. The Sigma-trial is a prospective, multi-center, double-blind, randomized study. Patients with symptomatic diverticulitis are randomized for either open or laparoscopic sigmoid resection. Our hypothesis is that patients undergoing laparoscopic sigmoid resection have fewer complications, less pain and earlier discharge from the hospital.

### Endpoints

Primary endpoints of the study are postoperative morbidity and mortality. Minor complications are defined as wound infections, urine tract infections pneumonia, venous thrombosis or other. Major complications consist of anastomotic leakages, postoperative haemorrhage, intra-abdominal abscesses, re-operations and other within the first four postoperative weeks. Data concerning late complications after four weeks are collected at the outpatient clinic six months postoperative (i.e. incisional hernia, ileus or other).

The secondary endpoints are procedure related events such as duration of operation, conversion to open procedure in laparoscopic group, blood-loss during operation, number of re-admissions and re-operations. Furthermore postoperative recovery data are hospital stay (days), type and number of analgesics needed after operation, VAS-painscore, return to fluid and normal diet, postoperative ileus, SF-36 questionnaire (general health) translated and adapted to nationality, recurrence rate after five years.

### Power of the study

According to the published literature and own experience at the VU medical centre a difference in morbidity of 23% is found between the open procedure (35%) and the laparoscopic procedure (12%) [19-21]. To demonstrate this difference of 23%, using α = 0.05 and β = 0.2, two groups of 52 patients are required. This means that a total of 104 patients have to be included.

### Inclusion criteria

Patients who were admitted for a conservatively treated episode of diverticulitis, who will therefore undergo an elective resection of the sigmoid. The indication for elective resection is in patients < 50 years after one episode of conservatively treated diverticulitis and in patients older than 50 years after two episodes of diverticulitis or in case of progressive abdominal complaints due to strictures caused by a previous episode of diverticulits. Moreover patients with recurrence of bleeding are candidates for inclusion. The diagnosis diverticulitis is confirmed by CT-scan and/or barium enema and coloscopy.

Operation will take place at least after three months of the last attack of diverticulitis.

### Exclusion criteria

Exclusion criteria are signs of acute diverticulitis, previous infra umbilical laparotomy or previous colorectal surgery or no informed consent. Presence of a fistula is not considered as exclusion criteria.

### Participating surgeons and clinics

Complication rate, duration of operation and morbidity can be a result of the learning curve of the operating surgeon. To prevent surgeon bias, the open and laparoscopic operations have to be performed by surgeons experienced in both techniques. It is reported that after 15 operations, operating time decreases significantly which could be an indication of the end of the learning curve [22]. Therefore it is required that the participating surgeon has performed at least 15 laparoscopic sigmoid resections as well as 15 open sigmoid resections.

Five European academic and non-academic centres will participate in the study: Academisch Medisch Centrum, Amsterdam; Hospital Clinic, Barcelona; Central teaching Hospital, Forde; Waterland Ziekenhuis, Purmerend; and VU medical centre, Amsterdam.

### Randomization and blinding

The patient will be informed about the trial at the outpatient clinic. When informed consent is obtained, the patient will be randomised at the outpatient clinic. Randomization is performed by an internet randomization module. Participating surgeons are allowed to login to the secured Sigma-trial website, after filling out the randomization form immediate response with randomization number and type of operation is obtained.

In order to perform a double-blind study, the patient will not be informed which procedure he or she will undergo. Also the ward physician and nurses are not informed about the type of procedure. Patients will be put on the waiting list as indication: 'Sigma-trial', without verifying the type of operation. Postoperative an opaque dressing will be applied to cover the wounds for five days and the surgery details will be kept separate from the patient's notes. When the patient does not agree to participate he or she will undergo the standard procedure in the corresponding department.

### Data collection and statistics

Data are partially collected via a secured internet module, which is specially designed for the Sigma-trial, and via datasheets on paper, which are sent to the VU medical centre by mail. Data are collected daily until the day of discharge. Preoperatively, at six weeks and six months postoperatively the SF-36 questionnaire is filled in by the patient.

There will be regular contact between the study coordinators and the participating centres. One research fellow will monitor the data of every included patient. An SPSS-database will be created with all required parameters. Data analysis will be performed in accordance with the intention to treat principle. Groups will be compared using an Independent Samples T-test where appropriate, other wise a Willcoxon or Chi-square tests. Painscores will be analysed using repeated measures analysis.

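### The rule for comparing groups makes no provision for adjusting SF-36 for the preoperative score the trial collects, which costs precision on a secondary endpoint

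*Protocol article*

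**What the plan says.** The protocol article, Data collection and statistics, gives the SF-36 schedule: "Preoperatively, at six weeks and six months postoperatively the SF-36 questionnaire is filled in by the patient". The same section sets one rule for all group comparisons: "Groups will be compared using an Independent Samples T-test where appropriate, other wise a Willcoxon or Chi-square tests". It makes one exception: "Painscores will be analysed using repeated measures analysis". Nowhere does the article mention a covariate, baseline adjustment or change from baseline.

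The SF-36 is listed among the secondary outcomes in Endpoints ("SF-36 questionnaire (general health) translated and adapted to nationality"). The Background puts quality of life in the study aim, which is to compare the operations "in terms of post-operative morbidity, mortality and quality of life". The sample size in Power of the study rests on morbidity alone: "using α = 0.05 and β = 0.2, two groups of 52 patients are required". No power is stated for SF-36.

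**The concern.** A preoperative score is usually the best single predictor available for the same patient's later score. Adjusting for it removes the part of the between-patient variation that was there before surgery. The trial collects this score, yet the method it names makes no use of it as a covariate. The pain sentence shows that the authors considered a different method for one repeatedly measured outcome; SF-36, which has a true pre-treatment value, stays under the general rule.

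What is at stake is precision. The trial has 52 patients per arm, a number chosen for a large difference in a binary outcome. An SF-36 comparison at that size can detect only moderate differences, so an avoidably wide confidence interval matters for a stated part of the aim.

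**Working it through.** **The plan's own figure.** Inputs from Power of the study: 35% morbidity with open and 12% with laparoscopic surgery, α = 0.05 (taken as two-sided), power 80%. With the pooled-variance formula and no continuity correction, and mean rate (0.35 + 0.12)/2 = 0.235:

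n = [1.96·√(2·0.235·0.765) + 0.842·√(0.35·0.65 + 0.12·0.88)]² / 0.23² = 52.2 per group.

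This is 53 when rounded up, and power at 52 is 79.9%. The stated 52 per group reproduces. It concerns morbidity only, and nothing below changes it.

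**Inputs for SF-36.** From the document: 52 per arm, and scores before surgery, at six weeks and at six months. Assumed, because the document gives no SD and no correlation: a true difference of 0.5 SD, equal SDs at baseline and follow-up, complete data, two-sided α = 0.05, and r from 0.2 to 0.7.

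**Formulas.** In units of the follow-up variance, the variance per patient that enters the comparison is:

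- follow-up score only: 1
- change from baseline: 2(1 − r)
- ANCOVA on the preoperative score: 1 − r²

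Power comes from the noncentral t distribution with noncentrality (0.5/√variance)·√(52/2). For follow-up only this is 0.5·5.099 = 2.55, which gives 71.4%. For ANCOVA at r = 0.5 it is (0.5/√0.75)·5.099 = 2.94, which gives 83.0%.

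| r | ANCOVA variance, 1 − r² | Reduction | Power, follow-up only | Power, change score | Power, ANCOVA |
|---|---|---|---|---|---|
| 0.2 | 0.96 | 4% | 71% | 51% | 73% |
| 0.3 | 0.91 | 9% | 71% | 57% | 75% |
| 0.4 | 0.84 | 16% | 71% | 64% | 79% |
| 0.5 | 0.75 | 25% | 71% | 71% | 83% |
| 0.6 | 0.64 | 36% | 71% | 81% | 88% |
| 0.7 | 0.51 | 49% | 71% | 90% | 94% |

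In patient numbers, ANCOVA with 52 per arm is worth 52/(1 − r²) per arm analysed without adjustment: about 54 at r = 0.2, 69 at r = 0.5 and 102 at r = 0.7.

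**ANCOVA against change scores.** The variance ratio is (1 − r²)/[2(1 − r)] = (1 + r)/2, which is below 1 for every r below 1. A change-score test is also worse than ignoring the baseline when r is below 0.5, and equal to it at r = 0.5. Both readings of the two-sample rule are therefore less precise than ANCOVA over the whole range.

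**The case against.** The test sentence does not name the SF-36. It is one generic sentence for all endpoints, with the t-test to be used where appropriate. A t-test on change from the preoperative score would fit the wording and would use the baseline. A reader might infer that the plan throws the baseline away; the text does not establish that. What stands is narrower: no provision is made for adjustment, and the change-score reading does not recover the lost precision.

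The gain also depends on a correlation that has to be assumed. At r = 0.2 it is only two percentage points of power. If change scores were the intended analysis and r were 0.6, the improvement would be from 81% to 88%, not from 71%. The full range is therefore shown.

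A reader might also infer that chance baseline imbalance makes the unadjusted comparison wrong. It does not. Under randomisation the test is unbiased, and its standard error and type I error already allow for such imbalance.

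Finally, a reader might infer a multiplicity problem because no SF-36 scale or time point is singled out. The article does not say that every scale will be tested at both follow-ups, and a condensed article may leave that detail to the full protocol or analysis plan. The same allowance does not remove the present point, because here the article states a general method and is not merely silent.

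**Conclusion.** The point holds as a matter of efficiency, not validity. By default, SF-36 falls under a two-sample rule with no covariate, although a preoperative score is collected. For assumed r of 0.2 to 0.7, ANCOVA reduces the variance of the follow-up comparison by 4% to 49% (1 − 0.7² = 0.51 of the variance remains at the upper end). With 52 per arm and a 0.5 SD difference, it raises power from 71% to between 73% and 94%, and to 83% at r = 0.5. Change scores would give 51% to 90%. These figures rest on the assumed r, equal SDs and complete data.

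The consequence is confined to a secondary endpoint. The stated hypothesis covers complications, pain and discharge, and neither the morbidity comparison nor the total of 104 patients is affected. This is a worthwhile improvement, not a flaw that threatens the trial's conclusions.

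**What to change.** Add one sentence to Data collection and statistics: SF-36 scores at six weeks and six months will be compared between groups by ANCOVA, or by one mixed model covering both times, with the preoperative SF-36 score as covariate. Fix this before any analysis by treatment group, so that the choice cannot appear to depend on the results.

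The cost is the change of wording and about one degree of freedom. No additional patients, visits or questionnaires are needed.

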**Figure 2 F2:**
[figure not shown]
Placement of dressing.

The principles of the fast track protocol for major colonic and rectal surgery as described by Delaney et al, will be applied [23]. When a drain is placed it will be removed one day after surgery. Postoperative pain will be treated by "Patient Controlled Analgesia" intravenously (PCA), a pump with morphine until maximal 72 hours after the operation. Patient will be advised by the anaesthesiologist about the PCA pump. Morphine doses will be noted. Oral analgesia (Paracetamol: 4 times 1 gram/24 hour) is started two days after the operation. Bladder catheter will be removed the second day after the operation. The nasogastric tube will be removed before endotracheal extubation. Non-carbonated liquids are offered the evening after the operation. Patient can decide when he or she wants to extend the diet to blend and solid food when oral fluids are tolerated.

To regain early mobilisation, patients are encouraged to sit out of bed starting one day after the operation. Patient will be discharged when they pass stool, are able to drink, eat solid food, can walk and are comfortable with oral analgesia. Delay due to "social" reasons will be noted. An independent physician will decide when the patient is going to be discharged.

Follow-up is carried out at the outpatient clinic, patients will be routinely seen at six weeks and six months after the operation.

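### Pain scores appear to stop at discharge, which depends partly on pain; the unqualified repeated measures wording permits a complete-case analysis biased against laparoscopy

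*Protocol article*

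**What the plan says.** All from the Protocol article:

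- Data collection and statistics gives the whole pain analysis in one sentence: "Painscores will be analysed using repeated measures analysis". It names no model, no days and no handling of days after discharge. On software it says "An SPSS-database will be created with all required parameters". It also commits to intention to treat.
- The same section sets the collection period: "Data are collected daily until the day of discharge". The only patient-reported measure it places after discharge is the SF-36: "Preoperatively, at six weeks and six months postoperatively the SF-36 questionnaire is filled in by the patient".
- Postoperative management gives the discharge rule: "Patient will be discharged when they pass stool, are able to drink, eat solid food, can walk and are comfortable with oral analgesia". It also provides for removing the dressing early in patients who leave before day five, so discharge inside the first five days is foreseen.
- Study objectives states: "Our hypothesis is that patients undergoing laparoscopic sigmoid resection have fewer complications, less pain and earlier discharge from the hospital".
- Endpoints lists pain among the secondary recovery measures: "type and number of analgesics needed after operation, VAS-painscore, return to fluid and normal diet".

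**The concern.** Pain helps decide when a patient leaves, and leaving ends the scores. Patients who remain on later days are therefore, on average, those with more pain. If laparoscopic patients hurt less or recover faster, more of them leave early, and the few who remain are a more heavily selected group than their open counterparts. A comparison restricted to patients with a score on every day of the window then understates any benefit of laparoscopy on pain.

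Less pain is one of the trial's three named hypotheses. A reader of the results could not tell from the published plan which kind of repeated measures analysis was intended, and the two obvious kinds can give materially different answers on these data.

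**Working it through.** **Plan's own figure.** There is none for pain. The only sizing figure, 52 per arm, concerns morbidity and is not at issue here.

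**From the document.** Daily collection ends at discharge; comfort is one of several discharge criteria; less pain and earlier discharge are hypothesised for laparoscopy; 52 patients per arm. That VAS is scored daily is inferred from the general sentence on daily data.

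**Assumed, because the document gives no values.** Scale 0 to 10; open mean 5.5 on day 1, falling 0.45 per day; between-patient SD 1.3; within-patient SD 1.0; constant true gap (open minus laparoscopic) of 1.0 or 0.5; discharge possible daily from day 3, with logistic odds depending on pain and, in some runs, also on arm; 20,000 simulated patients per arm, so that the results show bias rather than chance.

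**Complete-case repeated-measures ANOVA, true gap 1.0:**

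| Discharge depends on | Days 1–5 | Days 1–7 |
|---|---|---|
| arm only, not pain | 1.00 | 1.07 |
| pain, weakly | 0.96 | 0.90 |
| pain, moderately | 0.83 | 0.67 |
| pain, strongly | 0.72 | 0.54 |
| pain, moderately, plus arm | 0.55 | 0.25 |
| unrecorded pain, strongly, plus large arm effect | 0.32 | −0.02 |

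The 1.07 in the first row rests on the 3% of laparoscopic patients who remained.

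Sample lost: in the moderate-plus-arm case, days 1–5 keep 79% of open and 45% of laparoscopic patients. At 52 per arm that is 0.79 × 52 ≈ 41 against 0.45 × 52 ≈ 23. With a strong pain link and no separate arm effect, retention still differs (79% against 61%), because the arm with less pain leaves sooner.

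**Smaller true gap, 0.5.** Moderate link plus arm effect: 0.17 (days 1–5) and −0.10 (days 1–7). Strong link plus arm effect: 0.04 and −0.24. Clear reversal appears only here: small gap, added arm effect and a window to day 7.

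**Other analyses of the same simulated data, true gap 1.0:**

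- Averages of day-by-day observed differences: 0.84 to 0.97 without an arm effect, 0.58 to 0.86 with one.
- Likelihood mixed model, unstructured covariance, all observed scores: 0.98 to 1.01 when discharge depends on recorded pain. When it depends on unrecorded pain, 0.95 to 0.97, or 0.92 to 0.97 with a strong added arm effect (0.76 on day 7 alone).
- Days 1–3 only, before anyone has left under these assumptions: the full gap by every method.

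**Second set of assumptions.** Scale 0 to 100; mean 50 falling 5.5 per day; SDs 12 and 9; 52 per arm; true advantage 8 points; discharge from day 3 depending on pain, with odds 2.7 times higher in the laparoscopic arm. Complete cases over days 1–5 gave 4.1 (4.1 / 8 = 0.51), keeping 58% of open and 24% of laparoscopic patients. The mixed model gave 7.8 and days 1–2 alone gave 8.3. With no true difference, complete cases made laparoscopy look 2.6 points worse; the mixed model and days 1–2 were within 0.1 of zero.

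Varying the strength of the pain link and the arm effect, still with a true advantage of 8 over days 1–5, moved the complete-case estimate from 7.8 (no pain link; 7.8 / 8 = 0.98) to 2.0 (strong link plus arm effect; 2.0 / 8 = 0.25). An early common window gave about 8 throughout.

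**The case against.** The strongest reply is that the article never says patients will be dropped. It mentions SPSS only as the database and names no procedure, window or listwise deletion. A mixed model is itself a repeated measures analysis, so the sentence as it stands is compatible with the nearly unbiased method. Model details are commonly left to an analysis plan, which is not shown. All of this stands. A reader might infer that the plan specifies a complete-case ANOVA, or that its analysis is biased as written; the document supports neither.

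Three further inferences also go too far:

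- That low pain causes the missing scores. Discharge also requires passing stool, drinking, eating and walking; an independent physician decides; and social delay occurs and is recorded. Each loosens the link between pain and discharge.
- That discharge differs by arm. Earlier laparoscopic discharge is the trial's hypothesis, not an established fact.
- That the pain difference would be reversed. That needed a small true gap, an added arm effect and a long window, all under complete-case analysis.

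The reply does not dispose of the point entirely. Ending daily data at an event that depends partly on pain is fixed in this document, and no later analysis plan can recover scores that were never taken. The intention-to-treat commitment sits badly with dropping patients who went home early, but it does not itself say how missing days are handled.

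**Conclusion.** The point holds as a weakness of wording. Collection that stops at a partly pain-dependent discharge, together with an unqualified method label, leaves open an analysis biased against laparoscopy on a named hypothesis. Under the assumptions shown, a complete-case analysis of days 1–5 returns anything from nearly all of the true difference (weak or no pain link) to about half or less (moderate or strong link plus earlier laparoscopic discharge). Where the trial would fall in that range cannot be known from the document.

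The direction does not depend on the particular scale or SDs, but it does need discharge to be linked to pain: with discharge depending on arm alone there was no material bias. The conclusion also rests on the inference that VAS follows the daily schedule and stops with it. Pain is secondary, so this is a change worth making rather than a threat to the trial's main result.

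**What to change.** Replace the sentence on pain scores with wording such as:

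*VAS pain scores will be compared by a linear mixed model with arm, day and arm-by-day interaction, and an unstructured covariance or a patient random effect, fitted to all available scores without listwise deletion. The main contrast is the mean difference between arms over fixed early postoperative days, named in advance, on which nearly all patients are still admitted. Later days are supportive.*

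The last day of the main window should be chosen without sight of pain results by arm, for example from length of stay pooled over both arms.

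Cost: wording only. No extra data are needed, and SPSS fits such models. The downside is that the main pain result then covers only the early postoperative period. That period overlaps with patient-controlled morphine, so the morphine doses the plan already records should be shown for the same days.
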